# Flopropione, a Cysteine Conjugate β-Lyase 1 Inhibitor, for Prevention of Cisplatin-Induced Nephrotoxicity: Protocol for a Randomized, Open-Label, Proof-of-Concept Phase 1 and 2a Trial

**DOI:** 10.2196/87907

**Published:** 2026-02-12

**Keywords:** cisplatin, cysteine conjugate-β lyase 1, flopropione, kidney injury molecule-1, KIM-1, liver-type fatty acid-binding protein, L-FABP, nephrotoxicity, neutrophil gelatinase-associated lipocalin, N-GAL

## Abstract

**Background:**

Cisplatin-induced nephrotoxicity (CIN) is a major dose-limiting adverse event that can lead to both acute and chronic kidney injury. The formation of thiol-cisplatin conjugates within renal tubular cells has been implicated as a key mechanism underlying CIN. Flopropione is an inhibitor of cysteine conjugate β-lyase 1, an enzyme that catalyzes the formation of the thiol-cisplatin conjugate, which might prevent CIN.

**Objective:**

We designed a clinical trial to evaluate the safety of flopropione in patients receiving cisplatin-based chemotherapy and explore its efficacy in preventing CIN.

**Methods:**

This is a phase 1 and 2a, single-center, randomized, open-label trial conducted in patients undergoing cisplatin therapy. Participants are randomized in a 5:2 ratio per cohort to receive either flopropione or no treatment. On the day of cisplatin administration, the flopropione group receives oral flopropione twice daily (80 mg in cohort 1, 160 mg in cohort 2, and 240 mg in cohort 3). On the following day, all cohorts receive 3 doses of 80 mg of oral flopropione. A step-up dose escalation design is adopted, progressing from cohort 1 to 3 after confirming safety at each level. The primary end point is the safety of flopropione use in combination with cisplatin; the secondary end points include changes in the levels of urinary biomarkers of nephrotoxicity such as neutrophil gelatinase-associated lipocalin, liver-type fatty acid-binding protein, and kidney injury molecule-1. Blood and urine samples are collected within 48 hours before cisplatin administration and at 24 hours, 48 hours, and 1 week after its initiation for safety and efficacy assessments.

**Results:**

The first participant was registered in July 2024. As of January 2026, participant registration is ongoing. The final participant will complete the study by March 2026. Publication of results is expected by March 2027.

**Conclusions:**

This study is expected to contribute to advances in preventive strategies for CIN by providing evidence that inhibition of cysteine conjugate β-lyase 1 by flopropione may attenuate CIN.

**Trial Registration:**

Japan Registry of Clinical Trials jRCTs041220021; https://jrct.mhlw.go.jp/en-latest-detail/jRCTs041220021

**International Registered Report Identifier (IRRID):**

DERR1-10.2196/87907

## Introduction

### Background

Nearly 5 decades have passed since cisplatin was approved in the United States in 1978, and it remains one of the most widely used and effective anticancer drugs worldwide [1]. Cisplatin exerts potent antitumor effects primarily through the formation of DNA cross-links, thereby inhibiting DNA replication and transcription. However, because its cytotoxic activity is not selective for cancer cells, cisplatin damages normal tissues and causes adverse effects, such as myelosuppression, ototoxicity, neurotoxicity, and nephrotoxicity, which often limit its clinical use [2]. Among these toxicities, nephrotoxicity is particularly significant as it can result in both acute and chronic kidney injury [3]. Cisplatin-induced nephrotoxicity (CIN) reportedly occurs in approximately 30% of the patients receiving cisplatin-based chemotherapy [4,5].

Hydration therapy can reduce the intratubular concentration of cisplatin, thereby lowering renal toxicity, and it is recognized as the globally established preventive method for CIN [6,7]. Particularly, recently developed short hydration protocols have offered comparable protective effects to conventional hydration while reducing patient burden and improving safety [8,9]. In addition, magnesium supplementation is used for preventing hypomagnesemia and mitigating the subsequent aggravation of renal dysfunction [10,11]. Use of osmotic diuretics, such as mannitol, has also been reported as a preventive strategy; however, their use might increase risk of nausea, vomiting, and potential deterioration in renal function, particularly in patients with comorbid diabetes mellitus or hypertension [12]. Although emerging preclinical evidence in animal and in vitro studies suggests that antioxidant-based agents, including riociguat, JP4-039, and amentoflavone, exert renoprotective effects against CIN, robust clinical data supporting their efficacy and safety are still lacking [13-15]. Thus, in addition to preventive strategies such as hydration therapy and magnesium supplementation, the development of novel prophylactic approaches for CIN is warranted.

One proposed mechanism underlying CIN involves the formation of a highly reactive thiol-cisplatin complex catalyzed by cysteine conjugate-β lyase 1 (CCBL1) in renal tubular cells [16,17]. We previously reported that 2′,4′,6′-trihydroxyacetophenone, a CCBL1 inhibitor, dose dependently suppressed cisplatin-induced increases in blood urea nitrogen (BUN) and serum creatinine levels and tubular cell damage and apoptosis in a CIN mouse model [18]. Flopropione (2′,4′,6′-trihydroxypropiofenone), identified concurrently with 2′,4′,6′-trihydroxyacetophenone as a CCBL1 inhibitor, exhibits comparable inhibitory activity in renal tubular cells and animal models ([name], unpublished data, April 2022). Flopropione was approved in Japan in 1978 for its antispasmodic effects in hepatobiliary and pancreatic diseases and urinary calculi [19]. Given its known safety profile and potential to inhibit CCBL1, flopropione may also confer protective effects against CIN.

Therefore, for the first time, a phase 1 and 2a clinical trial has been designed for patients initiating cisplatin therapy to obtain proof of concept for the efficacy and safety of flopropione in preventing CIN.

### Objective

This phase 1 and 2a clinical trial aims to primarily evaluate the safety of flopropione in patients receiving cisplatin-based chemotherapy while exploring preliminary efficacy and generating proof-of-concept evidence for its potential protective effect against CIN.

## Methods

### Study Design and Setting

This is a single-center, randomized, open-label trial conducted at Fujita Health University Hospital (Toyoake, Japan) in patients undergoing cisplatin therapy.

### Eligibility Criteria

Patients who meet all inclusion criteria and none of the exclusion criteria are eligible for enrollment (Textbox 1).

Inclusion and exclusion criteria.
**Inclusion criteria**
Provision of written informed consent before participation after receiving an adequate explanationAged 18 years or older at the time of consent acquisitionNo previous exposure to cisplatin-containing chemotherapyScheduled to receive cisplatin monotherapy or cisplatin in combination with up to 2 other anticancer agents (concurrent radiotherapy permitted) under inpatient careDiagnosed with lung cancer, head and neck cancer, or other malignancies scheduled to receive a cisplatin dose of 75 mg/m^2^ or higher
**Exclusion criteria**
Renal impairment (estimated glomerular filtration rate <60 mL/min/1.73 m^2^)Pregnancy or possibility of pregnancyBreastfeedingKnown hypersensitivity to flopropioneAny other condition deemed inappropriate for study participation by the principal investigator or subinvestigator

No predefined criteria are established for using preventive measures against CIN, including hydration, magnesium supplementation, or mannitol administration. However, at the participating institution, hydration is routinely implemented for managing patients undergoing cisplatin regimens at doses of 75 mg/m^2^ or higher. In addition, magnesium supplementation and mannitol administration are implemented, involving many of the applicable regimens.

### Intervention

#### Intervention Procedure

Eligible participants are randomized in a 5:2 ratio per cohort to receive either flopropione (flopropione group) or no treatment (control group). Participants in the flopropione group receive oral flopropione twice on day 1 (30 minutes before cisplatin administration and at least 4 hours after) and 3 times on day 2. To ensure participant safety, a step-up dosing approach is applied. The single-dose levels are 80 mg in cohort 1, 160 mg in cohort 2, and 240 mg in cohort 3 on day 1. Progression to the next cohort will occur only after confirming safety in the preceding cohort. On day 2, all participants in the flopropione group will receive 80 mg per dose 3 times daily at intervals of at least 4 hours. Blood and urine samples will be collected within 48 hours before cisplatin initiation and at 24 hours, 48 hours, and 1 week after initiation. Participants in the control group undergo the same procedures as those in the flopropione group and receive standard cisplatin-based chemotherapy but without receiving flopropione. Regarding the analysis, participants assigned to the control group among all cohorts will be pooled for evaluation, whereas participants in the flopropione group will be evaluated according to their assigned dose level. An overview of the study procedure is shown in Figure 1; the step-up dosing approach diagram is shown in Figure 2.

**Figure 1 figure1:**
[figure not shown]
Overview of the study procedure.

**Figure 2 figure2:**
[figure not shown]
Step-up dosing approach diagram.

#### Criteria for Discontinuation of the Protocol Treatment

Treatment will be discontinued if any of the following occur: (1) withdrawal of consent by the participant, (2) inability to continue follow-up, and (3) investigator’s judgment that discontinuation is necessary for safety or other reasons.

#### Prohibited Concomitant Drugs

The concomitant use of nonstudy flopropione is prohibited from 1 day before cisplatin initiation until the 1-week postadministration evaluation.

### End Points

#### Primary End Point

Because this is the first clinical use of flopropione in patients treated with cisplatin, the primary end point is safety. Safety will be assessed by the incidence of adverse events, including abnormal laboratory test results, occurring from study treatment initiation (or 30 minutes before cisplatin initiation in the control group) until 1 week after cisplatin administration. Adverse events will be graded according to the Common Terminology Criteria for Adverse Events (CTCAE; version 4.0), while serious adverse events will be defined based on predefined seriousness criteria.

#### Secondary End Points

Secondary end points include changes in urinary biomarkers of nephrotoxicity—neutrophil gelatinase-associated lipocalin (N-GAL), liver-type fatty acid-binding protein (L-FABP), kidney injury molecule-1 (KIM-1), *N*-acetyl-β-d-glucosaminidase (NAG), β2-microglobulin, and α1-microglobulin—from baseline to 24 hours, 48 hours, and 1 week after cisplatin administration.

#### Exploratory End Points

Exploratory end points include the following:

Changes in serum creatinine, BUN, and estimated glomerular filtration rate from baseline to 24 hours, 48 hours, and 1 week after cisplatin initiationProportion of participants meeting the CTCAE grade 1 or higher acute kidney injury criteria (increase in serum creatinine of >0.3 mg/dL or 1.5 times above baseline) at 24 hours, 48 hours, and 1 weekNontargeted metabolomic analyses of serum and urine samples at each time point

### Study Schedule

The schedule for informed consent, registration, randomization, observations, and assessments is presented in Table 1.

**Table 1 table1:** Study schedule.

Items	Before cisplatin administration		After cisplatin administration		
	From 28 d before cisplatin administration (before visit)	Cisplatin administration day (visit 1)	24 h later (visit 2)	48 h later (visit 3)	1 wk later (visit 4)
Allowable visit windows	—^a^	—	–2 h to +2 h	–2 h to +2 h	–36 h to +36 h
Consent acquisition and registration	✓^b^	✓^b^			
Patient background	✓^b^	✓^b^			
Cisplatin administration		✓			
Flopropione treatment		✓^c^	✓^c^		
Blood and urine collection	✓^b,d^	✓^b,d^	✓	✓	✓
Regimen name and concomitant therapy	✓^e^	✓^e^	✓^e^	✓^e^	✓^e^
Adverse events		✓^f^	✓^f^	✓^f^	✓^f^

^a^Not applicable.

^b^Conduct at either the before visit or visit 1.

^c^The first dose is taken 30 minutes before starting cisplatin administration. On the day of administration, a second dose is taken at least 4 hours apart. On the second day, 3 doses of 80 mg are taken at least 4 hours apart.

^d^Data are collected from 48 hours before cisplatin administration until before starting the regimen.

^e^Data collection period is from registration to 1 week after cisplatin administration.

^f^Data are collected from the start of flopropione treatment (or 30 minutes before starting cisplatin administration in the control group) until the 1-week evaluation point or until discontinuation. As much data as possible are collected at the discontinuation point. If adverse events persist, observation is continued until recovery or until the principal investigator or equivalent determines follow-up is unnecessary.

### Eligibility Assessment

Eligibility will be confirmed within 28 days before cisplatin initiation. Baseline characteristics, including age, sex, height, weight, and comorbidities, will be recorded at registration.

### Registration and Random Allocation

After confirming eligibility, registration and randomization will be performed through an electronic data capture system, assigning participants in a 5:2 ratio (flopropione:control) within each cohort.

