### Limitations

This study has several limitations. First, it is an open-label study using a nontreated control group rather than a placebo control. Although the primary focus is on safety and biomarker evaluation, the potential for participant- or investigator-related bias cannot be completely eliminated. Therefore, a future pivotal study should adopt a randomized, double-blind, placebo-controlled design. Second, this study does not assess the impact of flopropione on cisplatin efficacy. Because this is the first clinical investigation of flopropione used in combination with cisplatin, it is limited to the first cisplatin administration (cycle 1) with an observation period of 1 week. Evaluation of potential effects on antitumor efficacy will require a longer observation period. Third, several studies have suggested that nephrotoxicity develops in a cumulative, dose-dependent manner [27,28]. Therefore, CIN may not necessarily occur after a single cisplatin administration. Accordingly, future studies involving multiple cycles of cisplatin and repeated treatment of flopropione will be necessary for comprehensively assessing its safety and preventive efficacy.

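### Open-label allocation can precede the baseline sample and cisplatin by up to 28 days, leaving time for arm-dependent withdrawal and co-protection

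*Protocol article*

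**What the plan says.** Five parts of the protocol article bear on the sequence.

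- **Randomisation.** Registration and Random Allocation: "After confirming eligibility, registration and randomization will be performed through an electronic data capture system", in a 5:2 ratio within each cohort. The two acts are described as one step, and no day is given.
- **Eligibility and registration.** Eligibility Assessment: "Eligibility will be confirmed within 28 days before cisplatin initiation". In Table 1 the row for consent and registration is ticked both for the pre-visit, which opens 28 days before cisplatin, and for the cisplatin day. Its footnote reads: "Conduct at either the before visit or visit 1". The sentence introducing Table 1 says that it covers randomisation, but the table has no such row.
- **Baseline.** Footnote d of Table 1, on blood and urine: "Data are collected from 48 hours before cisplatin administration until before starting the regimen".
- **Masking and co-protection.** The Limitations section states that "it is an open-label study using a nontreated control group rather than a placebo control". Under Eligibility Criteria: "No predefined criteria are established for using preventive measures against CIN, including hydration, magnesium supplementation, or mannitol administration". The same paragraph adds that at this site "hydration is routinely implemented for managing patients undergoing cisplatin regimens" at 75 mg/m² or more, and that magnesium and mannitol are given in many, though not all, of the regimens.
- **Analysis set.** Under Full Analysis Set, controls count if they receive cisplatin and flopropione patients count if they receive flopropione. Flopropione patients who never take it are left out.

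**The concern.** Normally the baseline is measured before anyone knows the arm, and the time between allocation and first treatment is kept short. Here neither is secured. For a patient registered early, the baseline of every urinary biomarker, creatinine, BUN, eGFR and the metabolome is taken after allocation, and the patient and treating team may have known the arm for weeks.

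Two things can happen in that interval. First, patients may leave for reasons linked to the arm, for example disappointment at being a control or second thoughts about an added drug. Those who leave before starting drop out of the analysis set, so the groups compared are no longer the groups randomised. Second, co-protection that is open to choice may be set with the arm known. The Introduction itself describes hydration, magnesium and mannitol as affecting renal outcome, so unequal use would act on the secondary and exploratory end points and could pass for a drug effect or hide one.

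**Working it through.** **Planned size.** 3 cohorts × (5 + 2) = 21 patients, of whom 3 × 5 = 15 receive flopropione and 3 × 2 = 6 are controls. 5/21 = 24% and 6/21 = 29%, as the Sample Size section states. There is no power calculation to reproduce, and the point does not depend on one.

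**Windows side by side** (days relative to cisplatin):

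| Step | Earliest | Latest |
|---|---|---|
| Eligibility, registration and, with it, randomisation | −28 | 0 |
| Baseline blood and urine | −2 (48 hours) | just before the regimen |
| Cisplatin | 0 | 0 |

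For a patient randomised on day −28:

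- baseline taken as soon as its window opens: 28 − 2 = 26 days after allocation;
- baseline taken just before the regimen: 28 − 0 = 28 days after allocation;
- cisplatin: 28 days after allocation.

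The longest interval to baseline is thus 28 days, and 26 days of it can pass before a baseline sample is even permitted. If registration takes place on the cisplatin day, the interval can be zero and the sample may come first. The article leaves the order open.

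**Weight of one patient.** 1/5 = 20% of a dose group; 1/6 = 17% of the pooled controls.

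**Illustration of unequal co-protection.** Suppose flopropione has no effect. With background risk p, relative risk r for a co-measure, and a difference d between arms in its use, the false risk difference is p × (1 − r) × d. The Introduction gives p of about 30%. The article gives neither r nor d, so ranges are assumed: r from 0.5 to 0.9, d from 0.2 to 0.6.

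- Smallest: 0.30 × 0.1 × 0.2 = 0.006, or 0.6 percentage points.
- Middle (r = 0.7, d = 0.4): 0.30 × 0.3 × 0.4 = 0.036, or 3.6 points.
- Largest: 0.30 × 0.5 × 0.6 = 0.09, or 9 points.

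The Limitations section warns that nephrotoxicity may not appear after a single cisplatin dose. The risk within this trial's week may therefore be below 30%, and the false difference would shrink in proportion.

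**After the fix.** If the baseline sample must come first, no part of the baseline follows allocation, and the longest interval from randomisation to cisplatin falls from 28 days to 2. The sample size stays at 21.

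**The case against.** The strongest reply is that the article gives an order but no day for randomisation, and that the moment of release may be fixed in the full protocol, which is not shown. That limits the claim to what this text permits. It does not remove it: the one timing statement ties randomisation to registration, and registration is expressly allowed from day −28.

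Three stronger readings are tempting, and the article does not support them.

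- **That co-protection is settled after allocation.** The article does not say when it is decided. Hydration is routine at the site, and magnesium and mannitol appear partly tied to the regimen, which is already scheduled at entry. The room for choice lies mainly in magnesium, mannitol and hydration volume.
- **That baseline values are biased by the known arm.** They are laboratory measurements taken before cisplatin and before any study flopropione. Knowledge of the arm can reach them only indirectly, through sampling time within the 48 hours, prior care, and who remains in the trial.
- **That slots will probably be lost and concurrent control halved.** If 5% to 10% of randomised patients never started and none were replaced, the chance of losing at least one of 21 would be 1 − 0.95^21 = 66% to 1 − 0.90^21 = 89%. For the 6 controls it would be 26% to 47%. But the article gives neither that rate nor a replacement rule. Controls are pooled, so one lost control is 1 of 6 in the analysis, even though it is 1 of 2 in its cohort.

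It is also fair to say that the Limitations section admits open-label bias in general, that concomitant therapy is recorded from registration to one week, that the primary end point is safety, and that no formal hypothesis testing is planned. These points lower the stakes. Recording lets an imbalance be described, not prevented, and the admitted limitation does not cover this avoidable sequence.

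**Conclusion.** The point holds in this form: the text allows open-label allocation up to 28 days before the baseline sample and before cisplatin, and nothing in the article prevents it. The consequences are an opportunity for arm-dependent withdrawal, which the analysis set then leaves out, and for discretionary co-protection to be chosen with the arm known.

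The 28 days is a maximum. How many patients were registered early is not known, and the article reports no actual imbalance. The size of any bias cannot be derived from it: the 0.6 to 9 percentage points above rest on assumed inputs. What is certain is that groups of 5 and 6 are too small to absorb even one patient handled differently. The change is worth making because it is cheap, but the present sequence does not invalidate the trial.

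**What to change.** 1. Keep consent and eligibility screening at up to 28 days, but separate randomisation from registration.
2. Release the allocation in the electronic data capture system only after baseline blood and urine have been collected within the existing 48-hour window, and before the first dose time.
3. Give randomisation its own row in Table 1, after baseline collection.
4. Enter the planned hydration, magnesium and mannitol before release, so that later changes can be described by arm. This does not prevent changes after allocation, and which measures to use stays with the investigators.
5. For patients already randomised, report by arm the interval from randomisation to baseline, the co-protection given, and anyone who left before starting.

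The cost is an altered data-capture step, a revised table and review-board approval of the amendment. No visit or sample is added. Flopropione would have to be dispensed at short notice, to patients treated as inpatients. Registration was still open in January 2026 and the last participant is due to finish by March 2026, so items 1 to 4 may reach few patients, and an amendment would leave two allocation procedures within 21 patients, which the report should state. Item 5 applies whatever is decided about the rest.
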